### Control group

Study participants in the control group will receive a one-time standardized 30-minute psycho-oncological consultation, including appropriate information material, as part of the AYA consultation at their study center. The t1 survey will also take place during this consultation. The t2 and t3 surveys will be conducted via e-mail or mail with appropriate invitations and reminders. A detailed study flow is shown in Fig. 2.

**Fig. 2 Fig2:**
[figure not shown]
Study flow

In the allocation or preference for the control condition, study participants receive a one-time standardized 30-minute counseling session with relevant information material in the AYA clinic at their study center. The t1 assessment also takes place during this AYA clinic counseling session. The t2 and t3 assessments will be conducted online or via postal mail with appropriate invitations or reminders.

### Eligibility criteria

#### Mentors

Study participants who act as mentors need to meet the following inclusion criteria: (1) a diagnosis of cancer at least 2 years before study inclusion; (2) current age and age at diagnosis between 18 and 39 years; (3) curative treatment approach; (4) ability to speak fluent German; (5) written informed consent to participate in this study; and (6) participation in a mentoring training. Patients will be excluded, if they are physically and mentally unable to participate in the study. To exclude mental disorders and suicidality, all mentors will be interviewed by a psychologist using the Structured Clinical Interview for DSM-5 Disorders - Clinician Version (SCID-5-CV) [53] before mentor training and the intervention (t0).

#### Mentees

Mentees are AYA patients undergoing acute treatment who receive emotional support and guidance from a mentor over a period of three months. All included mentees need to meet the following criteria: (1) diagnosis of cancer within the previous 6 months; (2) age between 18 and 39 years; (3) curative treatment approach; (4) ability to speak fluent German; and (5) written informed consent to participate in this study. Patients will be excluded, if they are physically and mentally unable to participate in the study and are undergoing psychotherapy. These criteria will be checked using electronic patient records and information provided by the treating oncologist.

### Randomization

The Comprehensive Cohort Design (CCD), or Patient Preference Trial, is an alternative to a randomized controlled trial. It is used when patient preference needs to be taken into account or when it is hypothesized that there is a relatively high preference for participation in a particular intervention [49, 54]. In the CCD, potential study participants are asked at the start of the trial if they agree to be randomized. If they agree, randomization takes place. If they refuse randomization, they can choose which study arm they will be assigned to. The CCD offers several advantages that are crucial for the successful implementation of this psycho-oncological intervention study, such as the possibility to include all potential study participants (including patients who refuse randomization) and a lower drop-out-rate in the control arm. If randomization is sufficient, an analysis similar to the RCT study is possible.

A limitation of the CCD is the difficulty in predicting the willingness of participants to be randomized. It is not possible to make clear statements about this in advance, especially as the present mentoring project is the first peer-supported intervention for young adult cancer patients in Germany.

If a sufficient number of study participants have been randomized in each study arm, analyses will be performed within the randomized arms and the non-randomized participants will be used to check external validity. If insufficient participants agree to randomization, all data will be analyzed as a prospective cohort study.

Potential study participants are fully informed about the study, the different study arms, and the main data to be collected. As a next step is to check the inclusion criteria and determine whether randomization can take place or whether there is a clear patient preference.

Randomization of study participants is performed within three working days by an independent documentation assistant of the Leipzig study center using the randomization software RITA. Block randomization with variable block length will be used to achieve a better balance. Stratification by gender and age will be performed for each study center to ensure structural equality for the intervention and control groups.

### Outcomes and measures

#### Primary outcome

Two standardized instruments are used to assess the extent to which the intervention contributes to an increase in self-efficacy (see Table 1). The hypothesis is that participants in the intervention group will report improved self-efficacy compared to participants in the control group (t2, t3), even three months after the intervention (t3).

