### Statistical analysis

#### Power and sample calculation

The number of cases was planned with the GPower program using a significance level of α = 0.05 and a power of (1-ß) = 0.8070. The primary outcome measure self-efficacy is used to demonstrate the effectiveness of the intervention. We make the following assumptions about changes in the intervention and control group: The pre-post effect size used is the effect size for self-efficacy.

d = 0.43, which could be found in the literature [68]. The expected controlled effect size requires a minimum of 90 subjects per group (180 subjects in total) measured with the U-test for independent groups. For this group size (*N* = 180), an analysis of variance with repeated measures (two groups, three measurements, correlation between measurements *r* = 0.5, epsilon = 1) can already demonstrate the following small effects: for comparisons between factors (IG vs. CG): f > 0.17; comparisons within factors (across measurement time points): f > 0. 09; and interaction effects between the two groups and time: f > 0.09. The sample thus has sufficient power to detect at least medium effects between the groups, as well as small effects within the groups and small interaction effects between the groups considering the measurement time points.

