#### Statistical methods

Quantitative data will be analyzed using the statistical program SPSS 29.0 [69]. First, the items of the scales of the primary and secondary outcomes are checked for missing values. Items and complete sociodemographic variables that violate the MCAR (missing completely at random) assumption are identified in each subanalysis using Little’s MCARTest. Missing values are then estimated using the Markov Chain Monte Carlo (MCMC) procedure. This procedure yields reliable results even with high proportions of missing values for both the MCAR and MAR (missing at random) missing value patterns. On the other hand, it is suitable for any patterns of missing values, but also for monotonic patterns.

Descriptive analyses are calculated for all variables and presented as frequencies, means, standard deviations and ranges. Sociodemographic and medical predictors of intervention effectiveness are identified using stepwise backward regression. Non-dichotomous categorical characteristics are first subjected to multifactorial analysis of variance. Games-Howell correction or Bonferroni-Holm correction is used as a post hoc test, as appropriate. Correlation analysis is performed prior to each regression to avoid multicollinearity. Mean comparisons using one-way factor repeated measures analyses of covariance (ANCOVA) are used to test the hypotheses.

The first step is to compare only the randomized groups. In the next step, the preference groups are analyzed to determine differences in the effects compared to the randomization groups. Finally, all four groups are compared with each other, adding an indicator variable (randomization/preference) as a covariate. If the number of randomized study participants is too small, the data must be analyzed as a prospective cohort study.

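### Two unranked primary instruments (GSE and CBI-B) at two follow-ups, but a sample size for one test at alpha 0.05 and no stated success rule

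*Protocol article*

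**What the plan says.** The Primary outcome section states: "Two standardized instruments are used to assess the extent to which the intervention contributes to an increase in self-efficacy". Two subsections follow, one for the 10-item GSE and one for the 14-item CBI-B, each with its own sum score. Secondary outcomes begin only after both. No composite of the two scales is defined and neither is placed ahead of the other. The hypothesis compares the intervention group with "participants in the control group (t2, t3), even three months after the intervention (t3"), so it covers both follow-ups.

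Power and sample calculation treats self-efficacy as one measure: "The primary outcome measure self-efficacy is used to demonstrate the effectiveness of the intervention". There is one significance level ("The number of cases was planned with the GPower program using a significance level of α = 0.05"), "a power of (1-ß) = 0.8070", one effect size ("d = 0.43, which could be found in the literature [68"]), which is not assigned to either scale, and one test ("measured with the U-test for independent groups"). The result is 90 per group, 180 in total.

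Statistical methods plans repeated-measures ANCOVA for the hypotheses. The only correction named is: "Games-Howell correction or Bonferroni-Holm correction is used as a post hoc test, as appropriate". It follows directly on the sentence about multi-category characteristics in the predictor analysis, and comes before the sentence on testing the hypotheses.

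**The concern.** The trial is sized for one confirmatory test, but the outcome it is meant to confirm is measured by two separately scored scales at two times. Without a rule for what counts as success, a significant result on whichever scale turns out better could be presented as showing that Peer2Me raises self-efficacy, and the choice could be made after the results are known. The Discussion looks ahead to proof of efficacy and to continuing the programme, so the confirmatory claim matters.

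The consequence depends on the rule eventually applied. A rule that lets either scale count raises the false-positive rate above 5%. A rule that demands both, or one that divides alpha, keeps the error rate but lowers power below the stated level.

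**Working it through.** **Inputs from the article.** Alpha 0.05, stated once; d = 0.43, taken as the between-group effect as the sample-size section does; 90 per group; 1:1 allocation; printed power 0.8070; correlation between repeated measurements 0.5; two instruments; follow-ups t2 and t3.

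**Assumptions.** Two-sided testing, which is not stated but reproduces the planned size (a one-sided U-test would need 71 per group for 80%). The correlation between GSE and CBI-B is not given, so a range of 0 to 0.8 is used. For joint power, d = 0.43 is assumed on both scales.

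**Step 1: the plan's own figure.** Power of the U-test from the noncentral t distribution, with the group size multiplied by the asymptotic relative efficiency 3/π:
- effective n = 90 × 3/π = 85.9 per group
- noncentrality = 0.43 × √(85.9/2) = 2.82; degrees of freedom = 2 × 85.9 − 2 = 169.9
- critical value at two-sided 0.05 = 1.974; power = 0.800

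The smallest group size reaching 0.80 is 90 (92 for 0.807). The stated 90 per group is therefore reproduced, as **one** two-sided test at 0.05.

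**Step 2: either scale suffices, one repeated-measures test per scale.** For independent scales the error is 1 − 0.95² = 9.75%. For correlated scales it is the probability that at least one of two standard normal statistics exceeds 1.96 in absolute value:

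| Between-scale correlation | Two-sided error | False claim of benefit (nominal 2.5%) |
|---|---|---|
| 0 | 9.75% | 4.9% |
| 0.3 | 9.5% | 4.8% |
| 0.5 | 9.1% | 4.5% |
| 0.7 | 8.3% | 4.2% |
| 0.8 | 7.8% | 3.9% |

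**Step 3: either scale at either time, four separate tests.** For four independent tests the error would be 1 − 0.95⁴ = 18.5%. With the article's correlation of 0.5 over time (simulation, 2,000,000 draws), it is 17.3% at between-scale correlation 0, 16.9% at 0.3, 16.2% at 0.5, 14.9% at 0.7 and 13.9% at 0.8. False claims of benefit are 8.1% at correlations 0.5 and 0.5.

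**Step 4: both scales required.** Both being significant cannot be more likely than one named scale being significant, so the error is at most 5%. Joint power at 90 per group, from a bivariate normal with marginal power 0.80:
- correlation 0: 0.80² = 0.64
- correlation 0.5: 0.69
- correlation 0.8: 0.73

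**Step 5: alpha divided over the two scales.** At 0.025 each the critical value rises to 2.261 and the power per scale at 90 per group falls to 0.71; 109 per group are needed for 0.80. Division over four tests (0.0125 each) gives 0.62.

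**The case against.** A reader might infer that the plan as written carries a type I error of 14-17%. The text does not support that. The figure needs separate tests at t2 and t3 and a rule that any one significant result is enough, and the article states neither. It plans repeated-measures ANCOVA, and the sample-size section describes a model with two groups and three measurements, which points to one model per scale. Hypothesis I, in the Aim section, speaks of an increase that then stays stable, which can be read as requiring the effect at both follow-ups. If both instruments were required as well, there would be no inflation at all. The percentages are also two-sided and so include false results in favour of the control group. These points stand, and they limit the size of the finding.

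It can also be said that the article is condensed, that endpoint hierarchy is often left to an analysis plan, and that Bonferroni-Holm is named. The accurate statement is therefore that no adjustment is *stated for the primary instruments*, not that none exists. The correction that is named is a post hoc one, placed with the categorical characteristics and not expressly tied to GSE, CBI-B, t2 or t3.

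What survives is more than a missing detail. The sample size depends on what the primary test is. The article gives two primary scales in one section and budgets for a single test in another.

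**Conclusion.** The point holds as a mismatch between the primary outcome and the sample size. The stated alpha and power hold together for one test at 90 per group, but not under any of the two-scale rules examined. If either scale counts, the error is about 8-10%. If both are required, power is about 0.64-0.73. If alpha is split over the scales, power is 0.71. The 14-17% figure is an upper case, conditional on four separate tests with any one counting, and should be reported only with that condition.

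Because no decision rule is given, the actual error rate is undetermined, from 5% or less up to that upper case. The ranges rest on an assumed between-scale correlation of 0 to 0.8, two-sided testing and normal approximations. The power figures use the plan's U-test; the planned ANCOVA could differ, depending on the correlation with baseline.

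**What to change.** Before outcome data are analysed, name one instrument and one contrast as the single primary test at two-sided 0.05. An example is the baseline-adjusted group difference at t2 from the planned repeated-measures ANCOVA. The instrument should preferably be the one to which the d = 0.43 assumption applies, if the sponsor can confirm that from its source; otherwise it should be chosen and justified on content.

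Test the remaining comparisons at 0.05 in a fixed, pre-stated order and stop at the first non-significant one. One possible order is the other instrument at t2, then the first instrument at t3, then the other at t3. State that the post hoc corrections do not govern these tests.

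This holds the error at 5% and keeps 90 per group and the planned power for the primary test, provided that d = 0.43 applies to the chosen contrast. It costs only wording. The drawback is that lower-ranked results cannot be claimed as confirmatory once an earlier step fails. Recruitment was scheduled to end in June 2024, just before publication in July 2024, so the designation should be dated and should record that no outcome comparison had been seen.

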#### General self-efficacy scale (GSE)

The validated German version of the General Self-Efficacy Scale is a self-administered instrument with 10 items for assessing a general sense of perceived self-efficacy with the aim to predict coping with daily hassles as well as to adapt various stressful life events [55]. It measures the expectation of subjective competence to act in the face of challenging situations such as cancer. A four-point Likert scale is used to determine the extent to which patients agree with the statements. The individual test score is calculated by summing up all items. Norm values of the German general population with an internal consistency of α = 0.92 and a sample of cancer patients with α > 0.90 are available [56, 57].

#### Cancer behavior inventory - brief version (CBI-B)

Self-efficacy in coping with cancer can be defined as a cancer patient’s confidence in his or her ability to develop adaptive coping behaviors. The German version of the short form of the Cancer Behavior Inventory (CBI-B-D) uses 14 items to describe coping behavior in the context of cancer [58]. Affected people estimate on a five-point Likert scale how confident they are in performing certain behaviors. By summing all 14 item-scores, a sum score is obtained, with higher scores indicating higher confidence in the ability to perform the coping behavior.

#### Secondary outcomes

As a secondary outcome, the data will provide information about the impact of the intervention on psychological distress (anxiety, depression), health literacy, life satisfaction, and social support on mentees (t1, t2, t3; see Table 1). The hypothesis is that participants in the intervention group will report less psychosocial distress, higher health literacy and life satisfaction and better social support compared to participants in the control group (t1, t2), even three months after the intervention (t3).

Similarly, for mentors, it is are expected that conclusions will be drawn on whether life satisfaction, empathy, and post-traumatic growth have changed after the 3 months of intervention (t1, t2).

#### Generalized anxiety scale (GAD-7)

The German version of the Generalized Anxiety Scale is a validated questionnaire that measures symptoms of generalized anxiety disorders and the symptom severity of generalized anxiety on a four-point Likert scale using seven items [59]. The individual item scores are summed to a total score, which can assume values between 0 and 21. The internal consistency in a representative German sample was α = 0.89 [60].

#### Patient health questionnaire (PHQ-9)

The Patient Health Questionnaire (depression module) measures depressive symptoms with nine items on a four-point Likert scale [61]. The PHQ-9 can be evaluated both categorically and by summing up the item characteristics. The scale sum value can reach values between 1 and 27.

#### European Health Literacy Survey Questionnaire (HLS-EU-Q16)

The HLS-EU-Q16 measures health literacy with 16 items and was developed from the long form of the HLS-EU-Q47 [62]. The items refer to various tasks and activities that are related to health care, disease prevention or health promotion. Respondents rate in each case how easy they think the corresponding task or activity is (“very easy,” “fairly easy,” “fairly difficult,” “very difficult”). A sum score from 0 to 16 can be calculated, and the latter can be classified as insufficient (< 9), problematic (9–12), and sufficient (13–16) health literacy.

#### Questionnaire of life satisfaction (FLZ-M)

The FLZ-M is a valid instrument that records the subjective assessment of satisfaction in various areas of life [63]. Life satisfaction is surveyed using the two modules “general life satisfaction” and “satisfaction with health”, each with eight items and an overall item. Subjective satisfaction and importance are assessed on a five-point Likert scale (0 = “dissatisfied” to 4 = “very satisfied”).

#### Berlin social support scales (BSSS)

The BSSS measure six dimensions of social support in a multidimensional approach: perceived social support, received social support, provided social support, need and search for social support, and protective cushioning in the sense of protecting others from stress [64]. Internal consistency was α = 0.8384 in a sample of *n* = 437 cancer patients.

#### Saarbrücken personality questionnaire on empathy (SPF)

The Saarbrücken Personality Questionnaire on Empathy is the German adaptation of the Interpersonal Reactivity Index [65, 66]. The SPF is a questionnaire for self-assessment of one’s own empathic abilities and consists of 16 items that measure both the cognitive and the emotional dimension of empathy on four subscales: imagination, empathic distress, empathic sympathy, and perspective taking. A five-point Likert scale (1 = “never” to 5 = “always”) is used to assess the extent to which the statements are true. Current norm values are available in age-graded tables.

#### Posttraumatic growth inventory (PTGI)

The Posttraumatic Growth Inventory (PTGI) measures the extent to which patients have experienced positive changes regarding cancer [67]. The questionnaire contains 21 items in five domains: new opportunities, relationship with others, personal strength, appreciation of life, and spiritual change. Using a five-point Likert scale, patients indicate the extent to which the item statements apply. Item scores are summed to a total score, with higher scores indicating higher posttraumatic growth. The PTGI is a reliable and valid instrument that has been translated into several languages.

**Table 1 Tab1:** Study instruments

	Screening t0		Baseline t1		follow-up t2		follow-up t3	
instrument	mentor	IG/CG	mentor	IG/CG	mentor	IG/CG	mentor	IG/CG
sociodemographic	X	X						X
clinical variables	X	X						X
psychosocial variables	X	X			X	X		X
SCID-5-CV	X							
GSE				X		X		X
PTGI			X		X			
SPF			X		X			
CBI-B				X		X		X
GAD-7				X		X		X
PHQ-9				X		X		X
BSSS				X		X		X
FLZ-M			X	X	X	X		X
HLS-EU-Q16				X		X		X

Notes. IG = intervention group (mentees), CG = control group, SCID-5-CV = Structured Clinical Interview for DSM-5 Disorders Clinician Version, GSE = General Self-Efficacy Scale, PTGI = Posttraumatic Growth Inventory, SPF = Saarbrücken Personality Questionnaire on Empathy, CBI-B = Cancer Behavior Inventory - Brief Version, GAD-7 = Generalized Anxiety Scale, PHQ-9 = Patient Health Questionnaire Depression Module, BSSS = Berlin Social Support Scales, FLZ-M = Questionnaire of life satisfaction, HLS-EU-Q16 = European Health Literacy Survey Questionnaire

As part of the study, sociodemographic data, including age, partnership status, number of children, and employment status, were collected from all participants at t1. Additionally, clinical variables—such as diagnosis, time of diagnosis, and therapies—were recorded through self-report. Psychosocial variables encompassed the utilization of psychosocial support services and general inquiries into mental health, all of which were also documented at t1.

### Statistical analysis

#### Power and sample calculation

The number of cases was planned with the GPower program using a significance level of α = 0.05 and a power of (1-ß) = 0.8070. The primary outcome measure self-efficacy is used to demonstrate the effectiveness of the intervention. We make the following assumptions about changes in the intervention and control group: The pre-post effect size used is the effect size for self-efficacy.

d = 0.43, which could be found in the literature [68]. The expected controlled effect size requires a minimum of 90 subjects per group (180 subjects in total) measured with the U-test for independent groups. For this group size (*N* = 180), an analysis of variance with repeated measures (two groups, three measurements, correlation between measurements *r* = 0.5, epsilon = 1) can already demonstrate the following small effects: for comparisons between factors (IG vs. CG): f > 0.17; comparisons within factors (across measurement time points): f > 0. 09; and interaction effects between the two groups and time: f > 0.09. The sample thus has sufficient power to detect at least medium effects between the groups, as well as small effects within the groups and small interaction effects between the groups considering the measurement time points.

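### The sample size takes d = 0.43, labelled a pre-post effect, unchanged as the between-group effect, with no control-group change stated

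*Protocol article*

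**What the plan says.** The section Power and sample calculation opens with "We make the following assumptions about changes in the intervention and control group". What follows is a single quantity: "The pre-post effect size used is the effect size for self-efficacy", with the value d = 0.43 attributed to a cited source. No figure for the control group appears. The text then states: "The expected controlled effect size requires a minimum of 90 subjects per group (180 subjects in total) measured with the U-test for independent groups".

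The section goes on to list effects detectable at N = 180 in a repeated-measures analysis of variance with r = 0.5: f > 0.17 between groups and f > 0.09 for the within-group and interaction effects.

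Under Control group, participants in that arm "will receive a one-time standardized 30-minute psycho-oncological consultation, including appropriate information material". Hypothesis I (Aim) compares Peer2Me with standard psycho-oncological care. Under Statistical methods, the hypotheses are to be tested by repeated-measures ANCOVA, not by the U-test.

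**The concern.** A pre-post effect size describes change within one group. A controlled effect size describes the difference in change between two groups. The first equals the second only when the control mean stays where it was. The paragraph moves from one to the other without a conversion, right after announcing assumptions for both arms.

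This is not a detail left to another document. The article presents the derivation, and its input changes meaning partway through. The comparator is a psycho-oncological consultation with information material, so zero control change is an assumption that needs to be stated and defended. At stake is the only calculation offered for 180 participants, and the power figure that readers will use when they interpret the result.

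**Working it through.** **Inputs.** From Power and sample calculation: α = 0.05, d = 0.43, U-test, 90 per group, r = 0.5. From Study design: 1:1 allocation. Sidedness is not stated; I take two-sided because it reproduces 90. Power is printed as 0.8070, which may be 0.80 with a stray citation number; 90 per group matches 0.80 (0.807 would need 92), and nothing below depends on it. The control-group gain c is not given; I assume 0.05 to 0.20 SD, in the same units as d.

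**Step 1: reproduce the plan's figure.** For the U-test with normal data, the effective size is n × 3/π, the noncentrality is d × √(n_eff / 2), and df = 2·n_eff − 2.

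- n = 90: n_eff = 85.94; noncentrality = 0.43 × √42.97 = 2.819; df = 169.9; critical t = 1.974; power = 0.8003.
- n = 89: power = 0.796. So 90 is the smallest n that reaches 80%.
- Variants for 80% power: two-sided t-test 86; one-sided U-test 71; two-sided U-test with minimum efficiency 100; two-sided U-test with logistic data 79. None gives 90.

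The between-group d that was entered is therefore 0.43 itself.

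**Step 2: allow for a control-group gain.** If 0.43 is the uncontrolled gain in the intervention arm, the between-group d is 0.43 − c.

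**Step 3: repeat for a baseline-adjusted analysis at r = 0.5.**

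- One follow-up: residual variance = 1 − 0.5² = 0.75, so the standardised effect is d / √0.75, in a two-sample t calculation at 90 per group.
- Mean of t2 and t3, assuming the same effect at both: variance of the mean = (1 + 0.5)/2 = 0.75; less 0.5² = 0.25 explained by baseline leaves 0.50; the standardised effect is d / √0.50.

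| Control gain c (assumed) | Between-group d | U-test power, 90 per group | Adjusted, one follow-up | Adjusted, mean of t2 and t3 | n per group for 80%, U-test |
|---|---|---|---|---|---|
| 0 | 0.43 | 80% | 91% | 98% | 90 |
| 0.05 | 0.38 | 70% | 83% | 95% | 115 |
| 0.10 | 0.33 | 58% | 72% | 88% | 152 |
| 0.15 | 0.28 | 45% | 58% | 75% | 211 |
| 0.20 | 0.23 | 32% | 43% | 58% | 312 |

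The difference detectable with 80% power at 90 per group is d = 0.43 (U-test), about 0.36 (adjusted, one follow-up) and about 0.30 (adjusted, mean of two).

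**Step 4: the standardiser.** A pre-post d may be scaled by the SD of change or by the raw SD. SD of change = SD × √(2(1 − r)), which equals the raw SD at r = 0.5. Under the plan's own correlation the choice does not matter.

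**Step 5: the repeated-measures figures.** At N = 180, 80% power and r = 0.5, I obtain f = 0.171 between groups and f = 0.095 within and for the interaction, in line with the plan.

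**The case against.** **The source value may already be controlled.** The cited source is not at hand, and the wording points both ways: the label says pre-post, while the lead-in mentions both groups and the sentence with the sample size calls the effect controlled. A reader might infer from the exact match at 90 that an uncontrolled effect was used. The match shows only that 0.43 was entered, not what 0.43 measures. This objection stands, and it makes the loss of power conditional on the label. It does not rescue the paragraph, because if the number is right the label is wrong.

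**The U-test is not the planned test.** This stands too. A reader might take 70 to 32% as the power of the planned analysis, but those figures belong to the U-test calculation. With baseline adjustment and one follow-up, a control gain of 0.05 SD still leaves 83%; averaging t2 and t3 keeps power above 80% up to a gain of 0.10 SD. The cushion is real but limited.

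**The detectable effects are already reported.** The article does give f values that do not rest on 0.43; f = 0.17 corresponds to d = 2 × 0.17 = 0.34, averaged over time points. They tell the reader what 180 participants can detect. They do not justify 0.43 as the difference to expect.

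**No document shows that controls will improve.** Correct. A reader might conclude that the trial has little chance of finding a realistic effect. The documents give neither a realistic between-group difference nor a control-group change in self-efficacy, so that conclusion has no support.

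**Conclusion.** The paragraph is wrong as written under either reading: the number is wrong if the label is right, and the label is wrong if the number is right. The calculation itself is correct; the fault lies in the unexplained identity of its input.

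If 0.43 is uncontrolled, the stated power of about 80% has no slack for any control-group gain. Over assumed gains of 0.05 to 0.20 SD, power falls to 70–32% for the U-test and 83–43% for a baseline-adjusted analysis of one follow-up. These figures rest on a two-sided test, 90 analysed per group, normal data, r = 0.5 and a range of control gains that is mine. If 0.43 is a between-group difference in change, no power is lost and only the wording needs correction.

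**What to change.** State whether d = 0.43 is a within-group pre-post effect or a between-group difference in change. If it is between-group, correct the label and leave the number.

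If it is uncontrolled:

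- state the assumed change in the control group and the resulting between-group d;
- restate power at 90 per group over a range of d (for example 0.23 to 0.43), for the planned ANCOVA as well as the U-test;
- present d = 0.43 (U-test), or about 0.36 (baseline-adjusted, one follow-up), as the difference the trial can detect, not the one it expects.

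The cost is the rewording of one paragraph. No extra patients are needed and neither conduct nor analysis changes. If the effect is uncontrolled, the downside is a less favourable stated power.
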